### Participants

Participants will be *N* = 96 Australian adolescents and young adults (48 per group), aged between 16 and 25 years, who self-report a current diagnosis of a CMC (for example arthritis, asthma, cancer, cystic fibrosis, diabetes, epilepsy, haemophilia, IBD, lupus, multiple sclerosis, and myalgic encephalomyelitis). Additional inclusion criteria are as follows (1) Australian resident; (2) fluent English speaker; (3) regular access to the Internet; (4) able to access online video and audio content.

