### Sample size

Using medium effect sizes, 40 participants per group are required for power = .80 and α = .05 [21]. To allow for typical treatment drop out of approximately ~ 15–20% [17] a target of 48 people per group has been set. This sample size is also sufficient to detect a medium effect for the purposes of the mediation analysis [27].

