**Fig. 1 Fig1:**
[figure not shown]
An overview of the Study Design

Following completion of the pre-test, participants will be randomised to conditions using the Qualtrics randomiser function. Participants in both arms of the trial will be contacted by a research assistant shortly after completing the baseline survey, who will inform them of their condition allocation, reiterate study procedures and answer any questions: as participants are recruited on a rolling basis, those assigned to SCO-CMC will receive access to the program as soon as the research assistant has made contact with them. At four and 12 weeks after completing baseline measures, all participants will be sent an email asking them to complete the outcome measure battery again. Following completion of the third set of measures, participants in the WLC will be contacted by the research assistant, who will provide a code for program access. All participants will receive up to two reminders to complete the measure battery at each time point; participants enrolled in the intervention will also receive an email or text reminder 2 weeks post enrolment to encourage them to continue progressing through the program.

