### Statistical analysis

#### Tests of intervention effects

We will perform Intention to Treat and Per Protocol analyses, conduct a sensitivity analysis [39], and compare complete cases versus cases lost to follow-up on baseline characteristics and scores on clinical measures, by randomisation group [64]. GLMM Mixed Model Repeated Measures will compare change in outcome measures across conditions, and time points, while controlling for random effects including age and gender. The group*time interaction will be calculated as a test of intervention effects. Using DASS-21 scores participants will be classified into outcome categories (Recovered, Improved, Unchanged, Deteriorated) according to Reliable Change Index and Clinical Significance of change at post-treatment and follow-up [32], to determine whether the SCO-CMC and control groups differ in clinically significant treatment outcome over time (Cochrane’s Q).

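### Cochran's Q cannot test whether the two arms differ in the Recovered/Improved/Unchanged/Deteriorated classification; the main group-by-time test is unaffected

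*Protocol article*

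**What the plan says.** In the protocol article, Statistical analysis – Tests of intervention effects, the main comparison is a repeated-measures mixed model. Its group-by-time interaction is declared to be the test of intervention effects. A further analysis follows: "Using DASS-21 scores participants will be classified into outcome categories (Recovered, Improved, Unchanged, Deteriorated"), assigned "according to Reliable Change Index and Clinical Significance of change at post-treatment and follow-up". Its stated purpose is to find whether the two groups "differ in clinically significant treatment outcome over time (Cochrane’s Q"). The test in that closing parenthesis, so spelled, is the only one named for the purpose.

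The design around it is a plain parallel-group trial. Under Recruitment, randomisation and allocation, "participants will be randomised to conditions using the Qualtrics randomiser function", with repeat measures four and 12 weeks after baseline. The Participants section gives "Australian adolescents and young adults (48 per group"). No matching of participants across arms is described, no rule reduces the four categories to two, and no other between-arm test is given for this classification.

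**The concern.** The question is whether two independent randomised groups differ on an ordered four-category outcome. The named test answers a different question: whether the proportion with a binary outcome is the same across several related measurements on the same people. Applied here, it would examine change between post-treatment and follow-up with the arms pooled, and only after the categories had been collapsed to two.

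What is at stake is the protocol's only stated by-arm comparison of recovery and deterioration. The test can be significant when the arms are identical but both change over time. It can be non-significant when the arms differ clearly and stably. A benefit reached by week 4 and held to week 12, which would be a good result for the programme, is the pattern the test cannot see.

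**Working it through.** No figure in the plan depends on this test, so there is nothing to reproduce. The check is of the test's structure, followed by an illustration.

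**Inputs from the protocol article**
- Two independent arms, 48 per group (Participants).
- 40 per group required before the dropout allowance, α = .05 (Sample size).
- Two classified time points and four categories (Tests of intervention effects).

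**Assumptions (not in the document)**
- The response rates.
- A latent within-person correlation between the two times of 0 to 0.8.
- For the illustration only, a binary outcome such as improved or not.

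**1. Structure.** Rows are persons and columns are the k related binary measurements, with column totals C_j and row totals R_i:

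Q = (k−1)[k ΣC_j² − (ΣC_j)²] / [k ΣR_i − ΣR_i²], on k−1 degrees of freedom.

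Arm appears nowhere. For k = 2, let a people be improved at both times, b at the first only, and c at the second only.
- Numerator: 2(C₁² + C₂²) − (C₁ + C₂)² = (C₁ − C₂)² = (b − c)².
- Denominator: 2(2a + b + c) − (4a + b + c) = b + c.

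So Q = (b − c)²/(b + c), which is McNemar's test of change from post-treatment to follow-up.

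**2. Other ways of applying it.** Running Q within each arm gives two time tests and still no arm comparison. Treating the arms as the related columns would need matched pairs, and the design has none. In every case the four categories must first become two.

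**3. Expected counts, 40 per arm (80 in all).** The 5% critical value on 1 df is 3.84.
- *Arms differ, 45% v 15% at both times.* Expected responders are 18 and 6 at each time, so C₁ = C₂ = 24 and Q = 0. The between-arm chi-square at one time is 80 × (18×34 − 6×22)² / (40×40×24×56) = 80 × 480² / 2,150,400 = 8.57.
- *Arms identical, both rising from 15% to 35%.* C₁ = 12 and C₂ = 28. At correlation 0, b = 80 × 0.15 × 0.65 = 7.8 and c = 80 × 0.35 × 0.85 = 23.8, so Q = (7.8 − 23.8)²/31.6 = 256/31.6 = 8.1. The between-arm chi-square on the expected counts is 0.

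**4. Rejection rates at α = .05, 40 per arm, correlation 0 to 0.8** (simulated, good to about one percentage point)

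| Assumed truth | Cochran's Q | Between-arm chi-square, one time |
|---|---|---|
| Identical arms, 15% → 35% | 84–99% | about 5% |
| Identical arms, 15% → 25% | 37–62% | about 5% |
| Identical arms, 15% → 20% | 14–21% | about 5% |
| 45% v 15% at both times | about 5% | 84–86% |

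The chi-square here is uncorrected; with a continuity correction its power is about 79%.

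**5. Second set of assumed rates (correlation 0.6, 40 and 48 per arm).** For a constant 50% v 20%, Q rejects in 6.2% and 5.4% of trials, against 81.8% and 88.5% for the chi-square. For identical arms rising from 20% to 40%, Q rejects in 94.3% and 97.1%, against 5.5% and 4.9%. The pattern does not depend on one choice of rates.

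**The case against.** Four points can be made for the plan.

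- **This is not the main analysis.** The declared test of intervention effects is the mixed model's group-by-time interaction. The aims and hypotheses do not mention clinically significant change, the sample size does not rest on it, and the trial calls itself exploratory. This stands in full. A reader might infer that the trial's conclusion about SCO-CMC versus waitlist is compromised. The document does not support that, because the interaction is a between-arm test and is untouched.
- **The name may be a slip.** The misspelling, and a purpose that concerns groups and categories, would fit another Cochran-type method such as Cochran-Mantel-Haenszel. That is possible, but the text does not say so. If it is so, the name still needs correcting.
- **The analyst would notice.** Q cannot be run on four categories, so the mismatch would probably surface before reporting. This lowers the risk of a false published result. It also means the test would then be chosen after the data are in hand, which is a reason to settle it now.
- **The rejection rates rest on invented rates.** This stands. A reader might take a figure above 90% as the trial's false-positive rate. It is not: it belongs to an assumed 20-point rise shared by both arms, and with a 5-point rise the rate is 14–21%. What does not depend on the rates is that Q ignores arm.

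A fuller analysis plan may hold more detail. That does not answer the point, which is not an omission: the article names a specific test, and that test does not fit the question it is given.

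**Conclusion.** The point holds as a defect of the clinical-significance analysis only. As written, the test cannot show whether the arms differ in the four-category classification: it has no arm term, it needs a binary outcome, and with two time points it is a within-person test of change. That conclusion follows from the formula and needs no assumption. The size is illustrative and depends on assumed response rates and a correlation of 0 to 0.8. With identical arms, rejection runs from 14% to 99% as the shared rise goes from 5 to 20 percentage points. Against a stable 30-point arm difference, rejection is about 5%, the test's null rate. A result from this test would leave a between-arm claim about recovery or deterioration unsupported, though not necessarily false.

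**What to change.** In Tests of intervention effects, replace Cochran's Q by a between-arm comparison of the categories at post-treatment and at follow-up. Ordinal logistic regression at each time point would do, or a chi-square or Fisher exact test if cells are sparse, as they may be with four categories and about 40 per arm. A proportional-odds mixed model with arm, time, arm × time and a participant random intercept is an option, not a requirement. Report the arm difference in the proportions reliably improved and reliably deteriorated, each with a 95% CI. If a different Cochran-type test was intended (for example Cochran-Mantel-Haenszel), name it and state the stratifying variable.

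The cost is analysis wording only: no new data, visits or participants, and no change to the mixed model.

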#### Mediating mechanisms

Mechanisms of action will be tested using multiple mediational analysis with bias-corrected bootstrap samples in MPlus, to test total and specific indirect effects. This is the most powerful test of mediation, requiring a sample of 71 participants to detect a medium effect [27].

#### Cost-utility analysis

CUA calculates the ratio between the costs of intervention and gains – in terms of quality-adjusted life years – against the costs and gains associated with a comparator. An incremental cost-utility ratio is calculated by dividing the incremental costs by the incremental effects using the following formula:

(mean Costs _intervention_ − mean Costs _comparator_)/(mean QALYs _intervention_ − mean QALYs _comparator_).

We will calculate the cost-utility of SCO-CMC compared with treatment as usual, from the perspective of the Australian health system. This assumes that the health system pays for the cost of the intervention and includes other costs covered by the health system only. We will calculate the cost of SCO-CMC using a bottom up approach. This will include the time taken for an assistant to enrol and contact participants as well as the cost of hosting the online program. Costs between baseline and follow-up will be calculated for each participant by summing costs measured using the resource use questionnaire and valued using Medical Benefits Schedule data (for visits to healthcare professionals), National Hospital Cost Data Collection data (for hospitalisations) and Pharmaceutical Benefits Schedule data (for pharmaceuticals). For the SCO-CMC group, total costs will also include the cost of the intervention. The number of QALYs per patient will be calculated by multiplying the AQoL-6D utility score by the appropriate time period. A base-case intention-to-treat analysis will be performed using all participants. To evaluate the impact of uncertainty on the cost and QALY estimates for each group, we will use bootstrapping with 5000 replications. These findings will be plotted on a cost-utility plane, which comprises four quadrants. We will also plot a cost-utility acceptability curve. This shows the probability that the intervention is SCO-CMC is cost-effective when compared with treatment as usual at different willingness-to-pay thresholds.

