#### Health resource use

A health resource use questionnaire was developed for the purposes of the study, based on the core items for a standardized resource use measure highlighted by Thorn et al. [61]. This measure asks about frequency of health service use, frequency and length of stay for hospital admissions, and frequency and dose of medication use over the past month. It will be used to collect resource use data for the purposes of the cost-utility analysis (CUA).

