### Procedure

#### Recruitment, randomisation and allocation

A diagram of the study design is shown in Fig. 1. Participants will be recruited from medical services and chronic illness networks; social media and online communities across Australia. Interested participants will be directed to a website which will outline study eligibility and will contain a link to the online consent form and screening measures. Participants who meet inclusion criteria will be randomly assigned a participant code, in order to link data across time points while preserving anonymity. They will proceed to an online pre-test questionnaire which will gather demographic and health resource use data (re-administered at post-test and follow-up), as well as the outcome measures. To promote retention participants will be informed that they will receive AUD$20 after completing the post-test surveys, and an additional $20 after they have completed the follow-up surveys. Participants will also be able to opt-in to receive a copy of the study results via email.

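### One-month recall at weeks 4 and 12 leaves about weeks 4 to 8 of the 12-week cost horizon unobserved, and the plan states no rule to fill it

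*Protocol article*

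**What the plan says.** Four statements in the protocol article bear on this.

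- **Recall period.** Outcome measures, Health resource use: the questionnaire records how often health services were used, plus "frequency and length of stay for hospital admissions, and frequency and dose of medication use over the past month". The same section names it as the data source for the cost-utility analysis.
- **Occasions.** Procedure, Recruitment, randomisation and allocation: resource use is collected at pre-test and "re-administered at post-test and follow-up". Randomisation comes after the pre-test.
- **Timing.** Same section, text after Fig. 1: the later measurements are requested "At four and 12 weeks after completing baseline measures".
- **Costing rule.** Statistical analysis, Cost-utility analysis: "Costs between baseline and follow-up will be calculated for each participant by summing costs measured using the resource use questionnaire". The intervention cost is added to the totals of the SCO-CMC arm. QALYs are the AQoL-6D utility multiplied by a time period whose length is not given. Uncertainty is assessed with 5000 bootstrap replications.

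The article mentions no scaling of a form to a longer interval, no interpolation, and no diary or linked claims data.

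**The concern.** The target is cost from baseline to follow-up, which is 12 weeks. The instrument looks back one month from week 4 and one month from week 12, so no form asks about roughly the second of the three months. A plain sum of the forms is not the quantity that the section says it is.

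The gap opens as the four-week programme ends, when a change in service use could plausibly show. If admissions share the one-month recall, an admission in those weeks is not recorded at all, and with 48 participants per arm a few admissions can move a mean cost. The bootstrap resamples whatever costs were recorded, so the cost-utility plane and the acceptability curve would carry the same gap without showing it. An analysis plan written later could extrapolate over these weeks, but it could not recover use that nobody was asked about.

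**Working it through.** The article gives no figure for cost coverage, so there is none to reproduce. The check is interval arithmetic.

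**Inputs.** Forms at day 0, day 28 and day 84 (Procedure). Recall of one month, m days (Health resource use). Horizon day 0 to day 84 (Cost-utility analysis). The article does not define a month in days, so m = 28 to 31 is an assumption.

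**Step 1: window of each form, [t − m, t], cut to days 0 to 84.**

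- Baseline form: days −m to 0, so nothing inside the horizon.
- Week-4 form: days 0 to 28. With m above 28 it also reaches back m − 28 days before baseline.
- Week-12 form: days 84 − m to 84.

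**Step 2: gap = (84 − m) − 28 = 56 − m days.**

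| m (days) | Days observed in horizon | Gap (days) | Gap / 84 | Gap ends at week |
|---|---|---|---|---|
| 28 | 56 | 28 | 33.3% | 8.0 |
| 30 | 58 | 26 | 31.0% | 7.7 |
| 31 | 59 | 25 | 29.8% | 7.6 |

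The gap starts at week 4 in every row. It is the same whether two or three forms are summed, because the baseline form adds no days inside the horizon.

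**Step 3: effect on mean cost per arm.** Assume a constant rate of use and a sum of the two post-baseline forms. The sum then represents 2m days of use against 84. The shortfall is 1 − 56/84 = 33.3% for m = 28, 1 − 60/84 = 28.6% for m = 30 and 1 − 62/84 = 26.2% for m = 31: about 30%. The last two are a little smaller than the gap because the week-4 form then also picks up 2 or 3 days before baseline.

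**Step 4: effect on incremental cost.** Take a 28-day month. Let C be the programme cost per participant, and let d1, d2 and d3 be the between-arm differences in mean health-service cost in weeks 0–4, 4–8 and 8–12.

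- True incremental cost: C + d1 + d2 + d3.
- Incremental cost from the sum: C + d1 + d3.
- Error: −d2.

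If the arms do not differ in weeks 4 to 8, d2 = 0 and there is no bias. If the programme saves a constant s per week, the true value is C − 12s and the sum gives C − 8s. Savings are then under-credited by 4s against a programme cost counted in full. If use rises instead, extra cost is under-counted. The sign is not known in advance.

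**Step 5: periods in the ratio.** If QALYs run over the full 12 weeks, they cover 12/52 = 0.231 years, against 8/52 = 0.154 years of observed cost (28-day month).

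**The case against.** **A journal article condenses the plan.** Summing may simply mean adding across resource types and forms, and a fuller analysis plan could weight each form to its interval. That is fair, and it rules out saying that the ratio and the acceptability curve must be wrong. It does not remove the point: the recall period and the survey dates are fixed in the article, and any later rule for weeks 4 to 8 would be extrapolation.

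**Recall may differ by item.** The one-month phrase could attach to medication alone, and the questionnaire is not shown. Reading it as covering all items is more natural, and no other period is given. On the narrow reading the gap is shown only for medication costs, and the worry about lost admissions is not established.

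**Three forms.** A reader might infer that all three questionnaires are summed, so that pre-randomisation cost enters the total. The article does not say so, and the phrase about costs between baseline and follow-up points the other way. This calls for a clarification; it is not an established error.

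**QALY period.** A reader might take the 12-week QALY horizon as stated. It is the natural reading given when participants are surveyed, but the length is not written down, so the mismatch in Step 5 is conditional.

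**Both arms share the gap.** This is true, and the 30% shortfall in each arm does not by itself bias the difference. It carries over to the health-service part of the incremental cost only if the between-arm difference is constant over time.

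**Standing of the analysis.** Cost-utility is a secondary aim of a trial described as exploratory, and the Discussion presents it as preliminary and as a pilot of resource-use methods. No efficacy comparison depends on it. This lowers the priority. A pilot of resource-use measurement is nevertheless poorly served by a form that misses nearly a third of the period.

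**Conclusion.** The point holds as a should-fix. As written, the costing rule does not give the cost between baseline and follow-up: about weeks 4 to 8 (25 to 28 of 84 days, 30% to 33%) have no resource use data, and no rule fills them. This rests on one-month recall applying to the items concerned and on forms at weeks 0, 4 and 12.

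The understatement of health-service costs by about 30% in each arm further assumes constant use and a sum of the two post-baseline forms. The error in incremental cost equals the unobserved between-arm difference in those weeks, so it may be zero and its direction is unknown. Costs and QALYs cover different periods only if QALYs run over all 12 weeks. It would go too far to conclude that the cost-utility result is bound to be wrong or that the efficacy conclusions are touched.

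**What to change.** 1. **Week-12 form.** Ask about the period since the week-4 survey, about 8 weeks, so that the two post-baseline forms together cover the horizon. This is one wording change in an online form. It costs more recall error over the longer period and, if made during rolling recruitment, leaves two versions of the form in use.
2. **Participants already surveyed on the one-month form.** State a rule for weeks 4 to 8, for example a cost equal to the mean of the observed week 0–4 and week 8–12 costs (28-day month). This is the same as multiplying their sum by 12/8 = 1.5. Add a sensitivity analysis that varies the assumed cost in the gap. If the form is left unchanged, apply this rule to everyone. It costs a sentence or two in the analysis section, but it remains extrapolation and will not capture an admission that fell in the gap.
3. **Baseline form.** State that its costs precede randomisation and are excluded from the sum. They can serve as a covariate in the cost comparison.
4. **QALY period.** State its length, so that costs and QALYs can be seen to cover the same interval.

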#### Quality of life

The Assessment of Quality of Life – 6 Dimension (AQoL-6D) is a generic, multi-attribute utility, preference-based measure that will be used to assess health-related quality of life [44]. It is an adaptation of the adult AQOL-6D utility instrument and has 20 items across six dimensions - independent living, mental health, coping, relationships, pain, and senses. There are scoring algorithms for both Australian adults and adolescents for the AQoL-6D [44].

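### The QALY rule does not say which utility score covers which period, and the incremental QALYs are an unadjusted difference in arm means although baseline utility is collected

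*Protocol article*

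**What the plan says.** All of this is in the protocol article; no separate analysis plan is shown.

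- **QALY rule** (Cost-utility analysis): each patient's QALYs are obtained by "multiplying the AQoL-6D utility score by the appropriate time period". Neither the score nor the period is identified, and no interpolation or area under the curve is named.
- **Denominator** (same section): "mean QALYs _intervention_ − mean QALYs _comparator", a difference of two arm means with no covariate.
- **Uncertainty** (same section): "we will use bootstrapping with 5000 replications", feeding a cost-utility plane and an acceptability curve.
- **Analysis set** (same section): "A base-case intention-to-treat analysis will be performed using all participants".
- **Instrument** (Quality of life): AQoL-6D, a "preference-based measure that will be used to assess health-related quality of life".
- **Timing** (Recruitment, randomisation and allocation): the pre-test gathers demographic and resource-use data "as well as the outcome measures", and the battery is repeated four and 12 weeks after baseline. Each participant therefore has up to three utility values, one of them from before randomisation.
- **Role** (Aims and hypotheses): cost-utility is a secondary aim.

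**The concern.** There are two separate weaknesses.

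First, a rule that multiplies one score by one period does not define a QALY when there are three scores and two unequal intervals (four and eight weeks). Several calculations fit the sentence and give different gains from the same data. Unless the rule is fixed beforehand, the choice remains open after the data are seen.

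Second, baseline utility is usually a strong predictor of later utility. With 48 per arm, the arms will differ somewhat at baseline by chance. An unadjusted difference in mean QALYs carries part of that difference into the denominator. Over a 12-week horizon the incremental QALYs are very small, so this noise can be of the same order as the effect. If the denominator changes sign, the point estimate moves to another quadrant of the plane and the ratio changes meaning. The bootstrap displays this uncertainty but does not reduce it. The efficacy model (Tests of intervention effects) works with change over time by arm and so takes account of baseline level; the cost-utility comparison, as printed, does not.

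**Working it through.** The article states no utility SD, correlation, gain or QALY figure, so there is nothing of its own to reproduce.

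**Inputs from the article.** Visits at weeks 0, 4 and 12; horizon 12/52 = 0.2308 years; 48 per arm (Participants).

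**Assumptions, not in the article.** Utility SD 0.20 (range 0.15–0.25); equal correlation between visits of 0.7 (range 0.5–0.8); true utility gain 0.05 (range 0.03–0.10), reached at week 4 and held, except in step 1; normal sampling distribution.

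**Step 1: what the rule can mean.** The trapezoid weights for weeks 0, 4 and 12 are 2/52, 6/52 and 4/52. Let u be the largest gain. The last three columns show each reading's gain as a multiple of the trapezoid gain.

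| Course of the effect | Trapezoid gain | Week-12 score × 12 weeks | Score at end of each interval | Score at start of each interval |
|---|---|---|---|---|
| Reached at week 4, held | 10u/52 | 12/10 = 1.20 | 12/10 = 1.20 | 8/10 = 0.80 |
| Linear rise to week 12 | 6u/52 | 12/6 = 2.00 | 9.33/6 = 1.56 | 2.67/6 = 0.44 |
| Reached at week 4, halved by week 12 | 8u/52 | 6/8 = 0.75 | 8/8 = 1.00 | 8/8 = 1.00 |
| Reached at week 4, gone by week 12 | 6u/52 | 0/6 = 0 | 4/6 = 0.67 | 8/6 = 1.33 |

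The error runs in both directions.

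**Step 2: size of chance imbalance.** SE of the baseline utility difference = 0.20 × √(2/48) = 0.041 (0.031–0.051 for SD 0.15–0.25). The part carried into the QALY difference depends on the correlation:

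- unadjusted trapezoid: 0.0408 × (2 + 0.7 × 10)/52 = 0.0071
- week-12 score × 12 weeks: 0.0408 × 0.7 × 12/52 = 0.0066

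The trapezoid alone therefore does not remove imbalance; it gives baseline utility a direct weight.

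**Step 3: precision with and without adjustment (trapezoid QALYs).**

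- Unadjusted variance per person = 0.20² × [0.3 × (4 + 36 + 16) + 0.7 × 144]/52² = 0.04 × 117.6/2704 = 0.001740. SE of the difference = √0.001740 × √(2/48) = 0.0085.
- Adjusted for baseline: residual variance 1 − 0.7² = 0.51 at each later visit, residual covariance 0.7 − 0.49 = 0.21. Variance = 0.04 × [0.51 × (36 + 16) + 2 × 0.21 × 24]/2704 = 0.04 × 36.6/2704 = 0.000541. SE = 0.0048.
- Variance reduction = 1 − 36.6/117.6 = 69%. At correlation 0.5 it is 1 − 51/100 = 49%.

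**Step 4: chance of a wrong-signed denominator.** For a gain of 0.05, the QALY gain is 0.05 × 10/52 = 0.0096. Unadjusted: z = 0.0096/0.0085 = 1.13, about 13%. Adjusted: z = 0.0096/0.0048 = 2.02 (from unrounded values), about 2%.

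| Change from the central case | SE unadjusted | SE adjusted | Wrong sign, unadjusted | Wrong sign, adjusted |
|---|---|---|---|---|
| None | 0.0085 | 0.0048 | 13% | 2% |
| SD 0.15 | 0.0064 | 0.0036 | 7% | 0.3% |
| SD 0.25 | 0.0106 | 0.0059 | 18% | 5% |
| Correlation 0.5 | 0.0079 | 0.0056 | 11% | 4% |
| Correlation 0.8 | 0.0088 | 0.0040 | 14% | 1% |
| Gain 0.03 | 0.0085 | 0.0048 | 25% | 11% |
| Gain 0.10 | 0.0085 | 0.0048 | 1% | below 0.1% |
| 40 per arm | 0.0093 | 0.0052 | 15% | 3% |

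**The case against.** A reader might infer that the plan overstates QALY gains. That needs the week-12 score to be applied to all 12 weeks, which the article does not say; its wording is equally open to interval-by-interval weighting. Even on the week-12 reading, step 1 shows overstatement only if the effect holds or builds. The programme lasts four weeks and is followed by eight weeks to the last assessment, so fading is plausible, and the same rule would then understate the gain.

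A reader might also infer that baseline imbalance biases the ratio, or passes into the QALYs in full. Neither follows. Under randomisation imbalance favours each arm equally often, so the unadjusted difference is unbiased, and the planned bootstrap shows the resulting uncertainty, sign included. Only part of the imbalance carries through, as step 2 shows.

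The size also depends on inputs that the article does not give. The Sample size section plans on medium effects. Read conventionally as half an SD, that is a utility gain of 0.10 at SD 0.20, where the risk of a wrong sign is about 1% even without adjustment. The cost-utility analysis is a secondary aim, and the Discussion describes its yield as preliminary.

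Finally, the printed ratio may be only a general definition, with interpolation and covariates left to a fuller plan. This has some force. But the section goes into detail on costing sources, the number of replications and the graphical output, and it states both a QALY rule and an estimator. The point is that those can be made exact and more precise at almost no cost, not that the article omits something it had to contain.

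**Conclusion.** The point holds as a specification and precision issue, not as a finding of bias. The QALY rule is ambiguous, and the readings tried give from 0 to 2 times the trapezoid gain, depending on the course of the effect. The unadjusted difference in means is valid but wastes information. Under the central assumptions, baseline adjustment cuts the standard error from 0.0085 to 0.0048 QALY and the chance of a wrong-signed denominator at a utility gain of 0.05 from about 13% to 2%. The benefit matters most for small gains or a large SD and is minor at a gain of 0.10. All these figures rest on an assumed SD, correlation and gain; the variance reduction depends only on the correlation pattern and visit times (49% to 69% at correlations of 0.5 to 0.7). The change is worth making, but the efficacy conclusions do not depend on it.

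**What to change.** In the Cost-utility analysis section:

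1. Define each participant's QALYs as the trapezoid area under the AQoL-6D utility curve: 2/52 × baseline + 6/52 × week-4 + 4/52 × week-12 utility.
2. Estimate incremental QALYs by linear regression of QALYs on arm with baseline utility as covariate, and use the arm coefficient as the ratio's denominator. This is the essential step, because the area under the curve alone does not remove imbalance.
3. Refit the regression in each of the 5,000 bootstrap replicates, and base the plane and the acceptability curve on the adjusted differences.

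This should be fixed before the outcome data are examined. It costs a few sentences of analysis text and a few lines of code. It needs no new data, visits or participants.
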